# Impact of different exercise training modalities on the coronary collateral circulation and plaque composition in patients with significant coronary artery disease (EXCITE trial): study protocol for a randomized controlled trial

**DOI:** 10.1186/1745-6215-13-167

**Published:** 2012-09-14

**Keywords:** Atherogenesis, Coronary artery disease, Coronary collateral blood flow, Collateral circulation, Exercise training, Interval training, Pathophysiology

## Abstract

**Background:**

Exercise training (ET) in addition to optimal medical therapy (OMT) in patients with stable coronary artery disease (CAD) has been demonstrated to be superior to percutaneous coronary interventions (PCI) with respect to the composite endpoint of death, myocardial infarction, stroke, revascularization and hospitalization due to worsening of angina. One mechanism leading to this superiority discussed in the literature is the increase in coronary collateral blood flow due to ET. Until now, data demonstrating the positive effect of ET on the collateral blood flow and the functional capacity of the coronary collateral circulation are still lacking.

**Methods/design:**

The EXCITE trial is a three-armed randomized, prospective, single-center, open-label, controlled study enrolling 60 patients with stable CAD and at least one significant coronary stenosis (fractional flow reserve ≤0.75). The study is designed to compare the influence and efficacy of two different 4-week ET programs [high-intensity interval trainings (IT) versus moderate-intensity exercise training (MT) in addition to OMT] versus OMT only on collateral blood flow (CBF). The primary efficacy endpoint is the change of the CBF of the target vessel after 4 weeks as assessed by coronary catheterization with a pressure wire during interruption of the antegrade flow of the target vessel by balloon occlusion. Secondary endpoints include the change in plaque composition as assessed by intravascular ultrasound (IVUS) after 4 weeks, myocardial perfusion as analyzed in MRI after 4 weeks and 12 months, peak oxygen uptake (V02 peak), change in endothelial function and biomarkers after 4 weeks, 3, 6 and 12 months. The safety endpoint addresses major adverse cardiovascular events (death from cardiovascular cause, myocardial infarction, stroke, TIA, target vessel revascularization or hospitalization) after 12 months.

**Discussion:**

The trial investigates whether ET for 4 weeks increases the CBF in patients with significant CAD compared to a sedentary control group. It also examines the impact of two intensities of ET on the CBF as well as the histological plaque composition. The trial started recruitment in June 2009 and will complete recruitment until June 2012. First results are expected in December 2012 (4-week follow-up), final results (12-month long-term secondary endpoint) in December 2013.

**Trial registration:**

Clinical trial registration information-URL: http://www.clinicaltrials.gov.

Unique identifier: NCT01209637

## Background

Coronary artery disease (CAD) still remains one of the leading causes of mortality in many countries with more than 17 million deaths worldwide (WHO 2008). CAD is a result of atherosclerosis, which has been interpreted to be due to endothelial dysfunction and inflammatory reaction [1,2]. Percutaneous coronary interventions (PCI) have been shown to be favorable with respect to major cardiac events in patients with acute coronary syndromes [3,4]. In patients with stable CAD, the benefits of coronary revascularization are less clear. In particular, there is no reported advantage with respect to major cardiovascular events and mortality compared to medical therapy only in patients with stable angina [5-10].

Several randomized trials compared PCI in addition to an optimal medical therapy (OMT) versus OMT only in patients with stable CAD. The COURAGE trial is the largest randomized study comparing an OMT only with a PCI plus OMT in patients with stable CAD. This milestone trial showed comparable efficacy between the two strategies with regard to a combined endpoint of death, myocardial infarction and stroke [11-16].

In contrast, Kastrati and co-workers published a meta-analysis of 17 randomized trials comparing OMT with a PCI-based invasive strategy in 7,513 patients with stable CAD and symptoms or signs of myocardial ischemia [17]. The major finding of this analysis was that PCI may improve patients’ long-term survival compared to OMT with a 20% reduction of the primary endpoint of all-cause death in the PCI group. However, of all the trials included, three also enrolled unstable patients presenting with acute coronary syndrome (DANAMI, TIME, SWISSI II).

Since the first description of the coronary collateral circulation by Blumgart et al. in 1948 [18], extensive investigations have been done to quantify the coronary circulation as well as to assess its anatomical contribution and functional capacity [19]. Berry and co-workers [20] reported the presence of coronary collateral anastomoses to be a prognostically important adaption in patients with CAD.

Seiler et al. [21] demonstrated reduced long-term mortality in patients with stable CAD and well-developed coronary collateral circulation. Moreover, in patients with acute ST elevation myocardial infarction, extensive collateral flow before reperfusion has been shown to be a predictor for a favorable long-term outcome [22].

### Exercise training and CAD

Physical activity has been well documented to reduce the cardiovascular event rate in a long-term perspective [23,24]. In particular, Myers and co-workers reported a strong inverse and graded reduction of mortality in healthy subjects and patients with known CAD with increased physical fitness [25,26].

As previously reported in a randomized trial enrolling 101 male participants, a combination of exercise training (ET) and OMT in patients with stable CAD was associated with a higher event-free survival and an increased maximal oxygen-uptake as compared to PCI + OMT after 1 year of treatment [27]. Several mechanisms are reported to be responsible for the improvement in event-free survival after ET. Besides a reduction of cardiovascular risk factors, an improvement of endothelial function was documented after 4 weeks of ET [28]. An increase of coronary collaterals was often hypothesized, but to date there are no prospective studies available demonstrating a beneficial effect of a specific therapy on the number of pre-existing coronary collaterals or an induction of angiogenesis of collateral vessels in human beings. However, currently no clear consensus exists about how the best physiological adaption can be achieved with different ET modalities regarding the coronary collateral blood flow (CBF) [interval training (IT) versus moderate-intensity continuous exercise training (MT)]. In a recently published review, a strategy of IT alone or in combination with resistance training resulted in significantly greater effects on cardiorespiratory fitness and endothelial function compared to MT [29]. Hambrecht et al. reported a regression of coronary lesions only in patients performing regular physical exercise 5–6 h/week expending an average of 2,200 kcal/week [30].

### Assessment of the collateral blood flow

In the past, there has been growing interest in investigating coronary collateralization [31,32], and several methods have been used to assess the CBF (angiographic guidance versus hemodynamic evaluation).

In 1995, Niebauer and co-workers published a randomized study comparing intensive exercise training of >3 h/week in addition to a low-fat diet with a sedentary control group in regard to the change of the collateral formation [33]. After 1 year, the study failed to show a difference in collateral blood supply between the two groups. This result might have been due to the angiographic evaluation of collateral vessels based only on QCA analysis.

In the 1990s, the method of measuring the fractional flow reserve (FFR) as an invasive pressure-derived index was reported by Pijls and De Bruyne [34,35]. This method allows a measurement of the pressure distal to a coronary stenosis.

Animal studies in healthy dogs [36,37] showed a significant increase in CBF in those who underwent treadmill training (75 min/day, 5 days/week) for 12 weeks. Beside a quantitative increase of collateral vessels, a growth of the diameter of epicardial collaterals was reported.

Compared to angiography-based QCA, measurement of the CBF after an artificial vessel occlusion with a coronary pressure wire seems to be a more functional approach to assess collateral vessels. This method was first described by Pijls et al. [35] as a quantitative assessment of recruitable CBF in human beings. In 120 consecutive patients undergoing elective coronary angiography, an invasive measurement of the mean arterial pressure (P_ao)_, coronary wedge pressure and central venous pressure (CVP) was performed at balloon inflations of 2 min (P_occlusion_). As described by Zbinden et al., the coronary flow index (CFI) is calculated as follows: $\left(P_{\text{occlusion}}-\text{CVP}\right)/\left(P_{\text{ao}}-\text{CVP}\right)$[38]. Zbinden and co-workers have demonstrated an increase of the collateral flow index of normal and stenotic vessels after 3 months of endurance training [35,38]. After PCI of the target vessel, a measurement of the CBF with a pressure wire under vessel occlusion with a balloon was performed. After successful PCI without residual stenosis, patients participated in an exercise program for up to 3 months three times a week. After 3 months, the prevention of existing collateral vessels after PCI with ET was reported. However, some limitations of the study need to be addressed. First, because of its non-randomized study design, a selection bias cannot be ruled out. Second, the initial coronary stenosis leading to angina and cardiac catheterization was treated by PCI before starting the ET program. By treating the stenosis, the ischemic trigger to increase angiogenesis might be reduced. This is partially explained by a reported increase of VEGF levels and circulating progenitor cells and an enhanced integration of EPCs into the endothelial cell layer after performing a 4-week ischemic ET program [39]. The authors did not report in how many patients a bare metal stent or a drug-eluting stent was implanted. This issue might have been important considering the initial worsening of endothelial function of PCI with a drug-eluting stent.

Buschmann et al. recently published a study analyzing the impact of treatment with external counterpulsation on the fractional flow reserve, and they reported a stimulation of coronary angiogenesis in patients with stable CAD after treatment with external counterpulsation for 7 weeks [40]. Again, the non-randomized study design and the lack of a real sham-group are limiting factors of the study.

Meier at al. [41] published a meta-analysis enrolling 6,529 subjects exploring the impact of coronary collaterals on mortality. It has been shown that the presence of high coronary collateralization indicates a 36% reduced mortality risk. The same research group reported a significantly reduced 10-year survival rate in patients with low CBF (CBF <0.25) compared to those with a well-developed collateral circulation (CBF ≥0.25) [42].

Pohl and co-workers [43] investigated the effect of dynamic handgrip exercise on the collateral blood flow in acute coronary occlusions. They found a significant increase of the CBF in patients undergoing PCI performing physical exercise for 3 min compared to a sedentary control group. The CBF was measured at the start and end of two 1-min coronary occlusions.

In addition, Wustmann et al. [44] elucidated the CBF in normal coronary arteries without stenotic lesions. They reported an immediately recruitable CBF that is sufficient to prevent myocardial ischemia during coronary balloon occlusion in 20% of patients without coronary stenosis.

Currently, little is known about the direct effect of physical exercise training on collateral formation, and the prognostic relevance of the CBF is still discussed controversially. Currently, there is no adequately powered clinical trial to assess the effect of different modalities of exercise training on the CBF (high-intensity IT versus MT) in addition to an OMT.

### Hypothesis

Therefore, the *Leipzig **EX**er**CI**se **T**raining versus M**E**dical Management* (EXCITE) trial is designed to test the hypothesis that a 4-week ET therapy in addition to OMT can increase coronary CBF compared to baseline measurements. In a second step analysis, the impact of different ET intensities (IT versus MT) on the change of CBF will be elucidated.

## Methods/design

### Study objectives

The EXCITE study is a three-armed, randomized, prospective, open-label, controlled trial in patients with stable CAD and a significant coronary artery stenosis of at least one major epicardial vessel. The severity of the coronary stenosis is assessed by measurement of the FFR. An FFR of ≤0.75 of at least one coronary stenosis is feasible for study inclusion. The aim of the study is to investigate the efficacy of 4 weeks of intensive exercise training in addition to OMT on the amount of CBF compared to a sedentary control group with OMT only. It will determine if exercise training is superior to standard medical therapy in increasing the CBF. Moreover, the Excite trial wants to demonstrate the superiority of a strategy of intensive interval exercise training compared to moderate-intensity exercise training. The trial is a proof-of-concept study and registered under http://www.clinicaltrial.gov: NCT01209637.

### Primary and secondary outcomes

The primary study endpoint of the EXCITE trial is the change in the coronary CBF index after 4 weeks of therapy among the three treatment groups (Table 1).

**Table 1 T1:** Primary and secondary endpoints

**Primary**	**Change in CBI after 4 weeks of treatment**
Secondary	1. Change in plaque morphology by virtual
	histology at 4 weeks as assessed by IVUS
	2. Change in myocardial perfusion at 4 weeks and
	12 months as assessed by adenosine MRI
	3. MACE at 1, 3, 6 and 12 months
	4. Hospitalization due to cardiovascular causes
	5. Change in atherosclerotic parameters (hs-CRP,
	ADMA, endostatin, EPC, ox LDL, cytokines,
	adiponectine), lipid status and glucose status
	6. Change in exercise capacity (ergospirometry) and
	V0_2_ peak

The secondary endpoints include the change in the tissue composition of the target lesion after 4 weeks of exercise training compared to optimal medical therapy only.

Other secondary endpoints are displayed in Table 1. To confirm a potential advantage by long-term follow-up, a 12-month follow-up will be performed in the course of the secondary endpoint evaluation.

Safety assessment includes bleeding complications related to the invasive measurement of the CBF according to the GUSTO criteria [45], stroke and renal failure.

### Patient population

The study population will consist of 60 patients with stable significant CAD enrolled at the University of Leipzig Heart Centre, Leipzig, Germany.

Patients are eligible if they are >18 and ≤75 years of age and have a significant coronary artery stenosis with a FFR ≤0.75 in at least one coronary artery.

The exclusion criteria reflect known contraindications for exercise training or application of adenosine. Eligible patients have to present with stable angina for at least 8 weeks and need to have ≥1 focal coronary luminal stenosis of more than 50% eligible for PCI. All patients have to be able to perform an ET program with a threshold of at least 50 Watts (W) without angina pectoris or signs of ischemia. Inclusion and exclusion criteria are demonstrated in Tables 2 and 3. Patients have to express willingness to participate in the study for 12 months. Patients presenting with a history of acute coronary syndromes within the past 2 months, significant valve disease, an LV ejection fraction of ≤40% or contraindications to adenosine stress are not eligible. In addition, patients with significant left main coronary disease or an ostial lesion are excluded.

**Table 2 T2:** Inclusion criteria

**Inclusion criteria**
1. Age >18 and <76 years
2. Stable angina pectoris CCS 1-3
3. Luminal stenosis of ≥50% in at least one major epicardial vessel eligible for PCI
4. FFR ≤0.75 in the target vessel
5. Angina threshold ≥50 W
6. Patients have to sign the informed consent form

**Table 3 T3:** Exclusion criteria

**Exclusion criteria**
1. Left main coronary artery stenosis >50%
2.High-grade stenosis (>75%) of the proximal left anterior descending artery
3. Stenosis with a minimum diameter of <2 mm
4. Acute coronary syndromes or recent myocardial infarction within the past 2 months
5. LV-EF ≤40%
6. Significant valvular heart disease
7. Pregnancy
8. Contraindication for application of adenosine:
AV block II and III°
Sick sinus syndrome
Long QT
Asthma bronchiale
9. Limitation of physical activity for reasons not due to coronary artery disease
10. Life expectancy <1 year
11 Substance abuse (drug or alcohol) problem within the previous 6 months

### Study examinations

After the patient has provided written informed consent, a cardiac catheterization with a clinical indication is performed. In case of a coronary artery stenosis >50%, a measurement of FFR will be performed. Only target vessels that are feasible for PCI with a minimum diameter of ≥2 mm will be included. Therefore, patients with a coronary stenosis of <2 mm will be excluded. Patients with an FFR of ≤0.75 will be enrolled in the study and randomly assigned by a computerized system in a 1:1:1 ratio to one of the three treatment groups (20 patients per group) with stratification according to age and sex. The study flow chart is shown in Figure 1.

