### Measurement of the coronary collateral circulation

The primary study endpoint (change in CBF) will be assessed by sensor-tipped guide wires during vessel occlusion with a balloon catheter for 1 min.

Therefore, a standard PCI balloon with a diameter 0.5 mm larger than the diameter of the target vessel is delivered via the FFR guide wire and will be inflated proximal to the coronary lesion within an angiographic healthy coronary segment with a low pressure of 4–6 atm to interrupt antegrade blood flow of the vessel during maximal hyperemia. Contrast dye is injected to show the interruption of the antegrade blood flow. During the measurement, the blood pressure of the target vessel distal to the coronary stenosis is continuously monitored as well as the systemic blood pressure.

To differentiate if the results after 4 weeks of therapy are due to CAD or physiological adaptations, the same measurements will be performed in a coronary vessel free of coronary stenosis (the reference vessel).

After 4 weeks of treatment, measurements will be repeated in the same coronary segments.

Cardiac catheterization as well as measurement of the CBF will be performed by three very experienced invasive cardiologists with expertise in hemodynamic analysis. Nevertheless, the procedure may carry some risks such as dissections of the coronary artery by the pressure wire, development of the thrombus burden, stroke or myocardial infarction during vessel occlusion. Application of adenosine intravenously can result in a complete atrioventricular block with short asystole.

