### Data and statistical analysis

In the absence of randomized trials and lacking data regarding ET and its impact on the collateral blood supply, a power calculation was not possible. Therefore, the Excite trial is designed to be a proof-of-concept study.

Categorical variables are presented as frequencies and percentages, continuous variables as means and standard deviations (SD), or medians and interquartile ranges for variables with skewed distributions. The primary endpoint will be analyzed according to the intention-to-treat principle using the Kruskal-Wallis test. In addition, event rates in all of these three treatment arms will be estimated (95% CI), and the time-to-event rates will be described using the Kaplan-Meier method. The secondary endpoints (Table 3) will be analyzed by appropriate methods according to data type to compare the three treatment arms. If statistically possible, pre-defined subgroup analyses will be performed including patients’ gender, presence of diabetes, amount of pre-existing CBF and FFR of the target lesion at baseline.

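### The primary Kruskal-Wallis test on change in CBF index is valid but uses neither baseline CBF nor the age and sex randomization factors, giving up precision at 20 patients per arm

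*Protocol article*

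**What the plan says.** All references are to the Protocol article.

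- Primary and secondary outcomes: the primary endpoint is "the change in the coronary CBF index after 4 weeks of therapy among the three treatment groups".
- Data and statistical analysis: "The primary endpoint will be analyzed according to the intention-to-treat principle using the Kruskal-Wallis test". No covariate or stratum is mentioned, and no adjusted analysis of this endpoint is described.
- Study examinations: patients are randomized "in a 1:1:1 ratio to one of the three treatment groups (20 patients per group) with stratification according to age and sex".
- Measurement of the coronary collateral circulation: "After 4 weeks of treatment, measurements will be repeated in the same coronary segments". The endpoint is a change, so a baseline value exists by design for each patient.
- Data and statistical analysis: baseline CBF and sex enter the analysis only through subgroup analyses, run where feasible, "including patients’ gender, presence of diabetes, amount of pre-existing CBF and FFR of the target lesion at baseline".
- On sample size, the same section says that "a power calculation was not possible".

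**The concern.** Two sources of information that the design already provides go unused. Baseline CBF is recorded in the same segment as the outcome and is likely to be its strongest predictor. Age and sex were thought important enough to stratify on, yet they play no part in the comparison.

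A change score subtracts the baseline with a coefficient of exactly 1. When the regression of the 4-week value on baseline has a slope below 1, part of any chance baseline difference between arms is carried into the comparison with its sign reversed. With 20 patients per arm such differences are not small. If age and sex predict change, balancing them by stratification and then ignoring them leaves their variation in the error term and makes the test somewhat conservative.

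At stake is the precision of the main comparison in a small trial in which each value requires an invasive catheterization.

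**Working it through.** **Inputs from the article.** Three arms of 20, and 3 × 20 = 60 agrees with the stated total. The endpoint is change in CBF index and the test is Kruskal-Wallis. No power, SD, effect size or correlation is given, so there is no power figure to reproduce.

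**Assumptions.** Equal SD at baseline and 4 weeks (set to 1), and a baseline/4-week correlation ρ of 0.3, 0.5, 0.7 or 0.9.

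**Step 1: variance.** Var(change) = 2(1 − ρ). Var(ANCOVA) = 1 − ρ². Their ratio is (1 + ρ)/2. The arm size that raw change would need to match ANCOVA at 20 is 20 divided by this ratio.

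| ρ | Var(change) | Var(ANCOVA) | Ratio | Reduction | Arm size needed |
|---|---|---|---|---|---|
| 0.3 | 1.40 | 0.91 | 0.65 | 35% | 30.8 |
| 0.5 | 1.00 | 0.75 | 0.75 | 25% | 26.7 |
| 0.7 | 0.60 | 0.51 | 0.85 | 15% | 23.5 |
| 0.9 | 0.20 | 0.19 | 0.95 | 5% | 21.1 |

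**Step 2: chance imbalance.** The SE of a baseline difference between two arms is √(2/20) = 0.32 SD. Under these assumptions, an imbalance of that size moves the change-score comparison by (1 − ρ) × 0.32, which is 0.16 SD at ρ = 0.5. Adjustment removes this shift.

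**Step 3: power on the same three-arm hypothesis.** Simulated with normal data, 20 per arm, two-sided 5%, both programmes 0.8 SD of change above control, and no age or sex effect. The last column is Quade's rank ANCOVA.

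| ρ | Kruskal-Wallis on change | ANCOVA F-test, baseline-adjusted | Quade |
|---|---|---|---|
| 0.3 | about 70% | about 89% | 87% |
| 0.5 | about 70% | about 84% | 81% |
| 0.7 | about 70% | about 79% | 73% |
| 0.9 | about 70% | about 74% | 65% |

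An unadjusted F-test on change is about 2 to 3 points above Kruskal-Wallis with normal data, so that much of each gap comes from the parametric test and the rest from baseline adjustment.

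**Step 4: age and sex.** A second simulation used a larger effect (0.9 SD of change in both programmes) and arms balanced on both factors. It assumed that age and sex each shift the 4-week value, but not the baseline, by 0.3 SD.

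| ρ | Kruskal-Wallis, null rejection | Kruskal-Wallis, power | ANCOVA with baseline, power | ANCOVA with baseline, age and sex, power |
|---|---|---|---|---|
| 0.3 | 4.6% | 79% | 94% | 95% |
| 0.5 | 4.7% | 80% | 91% | 93% |
| 0.7 | 4.2% | 77% | 85% | 87% |
| 0.9 | 2.8% | 71% | 75% | 84% |

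The fully adjusted test rejected about 5% under the null throughout. With no age or sex effect, adding the two terms changed power by 0.2 points or less.

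**The case against.** The strongest reply is that nothing here is wrong. Kruskal-Wallis on change is a legitimate comparison of randomized groups with controlled type I error. A rank test is a defensible choice for an index of unknown distribution with 20 per arm. The article calls the trial a proof-of-concept study and claims no power, so no stated target is missed. All of that stands. A reader might infer that the planned analysis is biased or inflates false positives; the article does not support that, and where strata are prognostic the error is in the conservative direction.

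It can also be said that a condensed article leaves covariates to the analysis plan. That carries less weight here, because the article names the primary test and that test cannot take covariates.

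The size of the gain is open. The same segments are measured again after only 4 weeks, so a high correlation is plausible, and at 0.9 the baseline gain is small. The argument for age and sex needs them to predict change: an effect on CBF that is the same at both visits cancels out. For correlations of 0.3 to 0.7 the assumed conservatism is negligible.

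Three stronger readings should be resisted:

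- A reader might set the 70% for Kruskal-Wallis against the 94%, 91% and 87% (at ρ = 0.3, 0.5 and 0.7) of a baseline-adjusted contrast of both exercise arms pooled against control. That comparison also changes the hypothesis from two degrees of freedom to one, so it overstates what adjustment brings.
- A reader might say that a change score over-corrects whenever the correlation is below 1. The slope is ρ × SD(4 weeks)/SD(baseline), so this holds in general only with equal SDs.
- A reader might extend the point to oxygen uptake, MRI and IVUS. The article fixes no method for those endpoints, so there is no stated choice to fault.

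**Conclusion.** The point holds as one of efficiency, not validity. The article fixes an unadjusted primary test while the design supplies a baseline measurement of the outcome and two stratification factors. Under equal SDs, normal data and an assumed correlation of 0.3 to 0.9, baseline adjustment reduces variance by 35% down to 5%. It raises three-arm power for a 0.8 SD effect from about 70% to between about 89% and 74%, including the 2 to 3 points that belong to the parametric test. The contribution of age and sex rests on an unproven prognostic effect. The change is worth making because it is free, but it is a recommended improvement and not a defect that undermines the trial's conclusions.

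**What to change.** Make the primary analysis an ANCOVA of the 4-week CBF index on treatment arm, baseline CBF index, age and sex, with the three-arm F-test and adjusted differences between arms with 95% confidence intervals. The endpoint itself need not change: with baseline in the model, the treatment estimates are identical whether the outcome is the 4-week value or the change.

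Keep Kruskal-Wallis on change as the distribution-free sensitivity analysis. Do not write in an automatic switch to Quade's rank ANCOVA for skewed data: in the simulation above it fell to 65% at a correlation of 0.9, below Kruskal-Wallis at about 70%.

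The cost is a revised sentence in the analysis section and a few lines of code. It needs no further patients or measurements. With one term each for age and sex, the model has 60 − 6 = 54 residual degrees of freedom, against 57 without covariates.
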